## Abstract

Exercise therapy is the most common approach for people with chronic neck pain (CNP). Although well‐established, it remains unknown which type of exercise is the best for treating this condition. Moreover, pain processing can play a role in the persistence of pain and in the response to interventions. Thus, the aim of this randomized controlled trial is to compare the acute and long‐term effects of two exercise protocols (specific and non‐specific) on pain and pain processing in individuals with CNP. One hundred and ten participants aged between 18 and 65 years who have had non‐specific neck pain for more than 3 months will be recruited. They will be randomized and allocated into two groups (specific exercises and non‐specific exercises) and both groups will perform an exercise programme twice a week for 8 weeks. Both programmes are divided into two progressive and individualized phases. The primary outcomes are change in pain intensity after 8 weeks of exercise and exercise‐induced hypoalgesia, and secondary outcomes are pressure pain threshold, temporal summation of pain, conditioned pain modulation, the Neck Disability Index, the Baecke Physical Activity Questionnaire, and the Global Perception of Change Scale. Outcomes will be assessed at baseline, after 8 weeks of intervention, and at 6‐month follow‐up.

## INTRODUCTION

1

Chronic neck pain (CNP) is the health condition that causes the fifth most disability in the world, and among musculoskeletal conditions, it is second only to low back pain (Vos et al., 2017). It affects 30–50% of the general population, mainly women, with a higher prevalence in middle age (Hogg‐Johnson et al., 2009). It is considered an important public health problem with great economic impact, impairment of productivity and absenteeism (Fandim et al., 2020; Hogg‐Johnson et al., 2009). Approximately, 50% of individuals who experience neck pain have had pain and disability for over a year, demonstrating poor recovery from the condition (Hush et al., 2011). The condition can be predicted by high initial levels of pain and disability, negative psychological factors, and a lower pressure pain threshold (PPT) (Fandim et al., 2020; Walton et al., 2009). In addition, individuals with CNP may have altered pain processing, measured by quantitative sensory testing (QST), and further investigations are needed since it can predict worse outcomes (Xie et al., 2020).

Currently, the literature recommends therapeutic exercises among treatment approaches for this population (Fandim et al., 2020; Gross et al., 2015). For chronic conditions, therapeutic exercises have proven to be an accessible and cost‐effective therapeutic modality (Boldt et al., 2014; Gross et al., 2015), although there is no consensus about the best type and dose of exercise (Blanpied et al., 2017; Villanueva‐Ruiz et al., 2022). Specific exercise (SE), described as exercising the painful area (Dueñas et al., 2021), is the most common type of exercise used in CNP, although it seems not to decrease local and remote pain sensitivity after a single bout of exercise (Naugle et al., 2012) – a phenomenon commonly known as exercise‐induced hypoalgesia (EIH; Koltyn et al., 2014). This hyperalgesia after exercise can be a major barrier to patient adherence to treatment, leading to physical inactivity and consequently worsening pain and disability (Jack et al., 2010).

On the other hand, non‐specific exercise (NSE), described as exercising the non‐painful area (Dueñas et al., 2021; Vaegter & Jones, 2020), seems to activate endogenous analgesic pathways (Naugle et al., 2012) and produce more EIH effects. It can be found in other chronic conditions such as knee osteoarthritis (Burrows et al., 2014) and shoulder myalgia (Lannersten & Kosek, 2010); however, in CNP, the EIH effect of NSE is not well established. In the last systematic review and meta‐analysis on this topic, Senarath et al. (2022) concluded that the evidence on EIH is conflicting and limited, caused by low methodological quality (Senarath et al., 2022; Vaegter & Jones, 2020). Besides this, SE cannot be considered superior to NSE in pain intensity and pain processing in CNP due to the small effect sizes and high risk of bias (Bontinck et al., 2024; Villanueva‐Ruiz et al., 2022), whether in acute or long‐term interventions (Hansen et al., 2022). It is also important to emphasize that the assessment of pain processing using QST, a method widely employed for this purpose (Xie et al., 2020), has not been well investigated in the area.

The primary aim of this randomized controlled trial (RCT) is to investigate if 8 weeks of NSE is superior in improving pain and EIH compared to SE in CNP. In addition, pain processing evaluated by QST will be compared between groups after the 8‐week intervention and at 6‐month follow‐up.

## METHODS

2

### Ethical approval

2.1

The study protocol has been approved by the Human Ethics Committee of the Federal University of São Carlos (UFSCar) under the following registration number: 67259123.0.0000.5504. It adheres to the guidelines set forth in Resolution 510/16 of the National Health Council concerning research involving human subjects. Informed consent will be obtained for all participants. The exercises described have minimal risk of adverse reactions, take place according to the usual clinical procedures, and are used only for people who speak and understand Brazilian Portuguese so that there are no language uncertainties in connection with the information provided. No placebo treatment is provided. For future inquiries regarding the data generated from this study, interested parties may contact the corresponding author, [name] with a reasonable request.

### Monitoring and auditing

2.2

This study does not have a formal data monitoring committee and no trial audit is planned as this trial does not investigate drugs or products. Adverse reactions will be discussed by all authors.

### Study design

2.3

This study protocol describes the design of a single‐blind RCT, developed in accordance with the recommendations of SPIRIT (Standard Protocol Items: Recommendations for Interventions Trials) (Chan et al., 2013), CONSORT (Consolidated Standards of Reporting Trials) (Moher et al., 2001) and TIDieR (Template for Intervention Description and Replication) (Hoffmann et al., 2014). This study was registered in the Brazilian Clinical Trials Registry (RBR‐337hq7s)—https://ensaiosclinicos.gov.br/rg/RBR‐337hq7s.

### Participants

2.4

Participants in this trial are women and men with chronic non‐specific neck pain.

#### Eligibility criteria

2.4.1

Participants between 18 and 65 years (Bernal‐Utrera et al., 2020), who speak and understand Brazilian Portuguese, experiencing non‐specific CNP (pain in the area between the nuchal line and the spinous process of the first thoracic vertebra without having a known cause; Fandim et al., 2020) for at least 3 months (Gattie et al., 2021), with pain at rest and/or a neck active movement score of ≥3 on a numeric pain rating scale (NPRS) (Rampazo et al., 2021) and ≥10 points (20%) on the Neck Disability Index (NDI) (Daher et al., 2020; Gattie et al., 2021) will be included. Participants may have other pain complaints as long as neck pain is predominant.

#### Exclusion criteria

2.4.2

Signs of radiculopathy will be verified by the Upper Limb Tension test, the Spurling test, the Traction/Distraction test (Bier et al., 2018), a history of radicular pain worse in the arm than in the neck, and the presence of paresthesia or numbness and/or weakness and/or altered reflex (Lam et al., 2022). Whiplash‐associated disorders, cervicogenic headache, fibromyalgia, pregnancy, history of trauma, cervical fractures or surgeries, inflammatory rheumatic diseases related to the cervical region, neurological disorders, tumors, and/or medical contraindication to physical exercise (Bernal‐Utrera et al., 2020; Daher et al., 2020; Gattie et al., 2021; Rampazo et al., 2021) will be also excluded. Individuals who received physiotherapy or cervical infiltration in the last 3 months, initiated some physical activity in the last 2 weeks, or used analgesics, anti‐inflammatory drugs or muscle relaxants acutely within 24 h before the evaluation will also be excluded (Rampazo et al., 2021, 2020).

### Recruitment procedure

2.5

Recruitment will take place through the dissemination of advertisements in social media networks, local newspapers and television. An online form will assess eligibility criteria, followed by a face‐to‐face visit for confirmation and informed consent. When eligible participants consent to participate, they will be randomized to one of the two exercise groups.

### Randomization and blinding

2.6

Electronic randomization will be performed (https://www.randomizer.org/) by a researcher not involved in the assessments or intervention. The allocation will be hidden in opaque, sealed and consecutively numbered envelopes stored securely. The therapist will open the sealed envelope in front of the participant before starting the intervention. Due to the nature of interventions (exercises), it is not possible to blind the physiotherapist. However, the evaluator will be blinded to the treatment group, and physiotherapists involved in treatment will be blinded to evaluation results. The effectiveness of blinding will be assessed after the 6‐month follow‐up. The researcher will record responses indicating whether she thinks the participant received SE, NSE, or if she does not know how to evaluate blinding effectiveness (Coppieters et al., 2021).

### Exercise interventions

2.7

Both groups will follow a home‐based exercise programme comprising stretching, mobility and strengthening exercises (Price et al., 2021) lasting 24 exercise sessions over 8 weeks, with a weekly frequency of three sessions, each lasting approximately 30 min, as recommended in guidelines (Booth et al., 2017; Ferro Moura Franco et al., 2021). The exercise programmes will be explained, and videos previously recorded with all the instructions needed will be provided.

Both groups will perform a previous effective protocol for decreasing pain intensity. The SE group will perform a protocol adapted from Celenay et al. (2016), while the NSE group will perform a protocol targeting the main muscle groups of the lower limbs (Ferreira et al., 2007) (Table 1). The exercise dose will be individualized based on recommendations by Price et al. (2021), utilizing body weight or elastic bands (Andersen et al., 2011; Celenay et al., 2016). Throughout the intervention, the training load will progressively increase, adhering to the principle of progressive overload (Progression Models in Resistance Training for Healthy Adults, 2009). Participants are expected to advance the exercise load when they surpass the specified repetitions or classify the Perceived Effort with a score equal to or less than 6 on the BORG Scale (Iversen et al., 2018; Morishita et al., 2018). In addition, there will be two phases of progression. Following the intervention, participants will be encouraged to continue exercising using videos tailored to their randomized group (O'Riordan et al., 2014; Suni et al., 2017).

**TABLE 1 eph13680-tbl-0001:** Intervention protocol exercises for both groups (specific and non‐specific).

Type of exercise	Exercise	Dose
Specific exercise group		
Phase 1 (weeks 1–4)		
Mobility/flexibility	Thoracic and cervical mobility on four supports	Two sets of 8–10 repetitions each
Strengthening	Cervical flexion in supine position	Three sets of 8–10 repetitions each
	Cervical extension in prone position	
	Scapular retraction with arms extended in prone position	
	Lateral shoulder raise	
Mobility/flexibility	Stretching for cervical extensors	One set lasting 30 s
	Stretching for cervical tilters and rotators	One set lasting 30 s

Phase 2 (weeks 5–8)		
Mobility/flexibility	Thoracic rotation in lateral decubitus	Two sets of 8–10 repetitions each
Strengthening	Cervical flexion with craniocervical flexion in supine position	Three sets of 8–10 repetitions each
	Cervical extension with elastic band in prone position	
	Scapular retraction and horizontal shoulder abduction with elastic band while standing	
	Shoulder abduction and elbow extension (Arnold shoulder press)	
Mobility/flexibility	Stretching for cervical extensors	One set lasting 30 s
	Stretching for cervical tilters and rotators	

Non‐specific exercise group		
Phase 1 (weeks 1–4)		
Mobility/flexibility	Flexion of hips and knees in supine position	Two sets of 8–10 repetitions each
Strengthening	Wall squat	Three sets of 8–10 repetitions each
	Hip abduction with elastic band seated	
	Hip raise in supine position (bridge exercise)	
	Extended leg raise in supine position	
Mobility/flexibility	Stretching for hip flexors	One set with 30 s of duration
	Stretching for hip extensors	One set with 30 s of duration

Phase 2 (weeks 5–8)		
Mobility/flexibility	Half‐kneeling hip mobility	Two sets of 8–10 repetitions each
Strengthening	Lunge	Three sets of 8–10 repetitions each
	Squat with hip abduction with elastic band (side lunge)	
	Unilateral hip raise in supine position (unilateral bridge)	
	Hip and knee flexion with elastic band while standing	
Mobility/flexibility	Stretching for hip flexors	One set lasting 30 s
	Stretching for hip extensors	

### Data collection procedure

2.8

Data collection, physical examination and QST will be conducted by a blinded evaluator.

### Outcomes

2.9

Outcome assessments will be performed at baseline, post‐intervention (8 weeks), and 6‐month follow‐up (Figure 1). For all assessments, participants will be instructed to avoid alcoholic and caffeinated beverages 24 h before the scheduled date (Marcuzzi et al., 2017). The evaluation room will be maintained at an approximate temperature of 23°C and without noise (Marcuzzi et al., 2017).

**FIGURE 1 eph13680-fig-0001:**
[figure not shown]
Flowchart summarizing experimental procedures.

#### Primary outcomes

2.9.1

##### Pain intensity at rest and on movement

Pain intensity will be evaluated through the numerical pain rating scale (NPRS) (Ferreira‐Valente et al., 2011). This scale ranges from 0 (no pain) to 10 (worst possible pain) and will be questioned at rest (Celenay et al., 2016) and different active cervical movements (flexion, extension, inclinations and rotations) (Rampazo et al., 2020). The highest value will be used for analysis. The minimal clinically important difference (MCID) is 2.5 points on a scale of 0–10 (Pool et al., 2007).

##### Exercise‐induced hypoalgesia

The blinded evaluator will measure the PPT both before and immediately after the exercise (Figure 2). EIH will be calculated as the difference between PPT immediately after the exercise protocol and PPT before exercise at the points of left upper trapezius, left quadriceps femoris, and right low back (Hansen et al., 2022; Christensen et al., 2022; Vaegter et al., 2021) (Figure 2). A positive value reflects EIH, and a higher value indicates more effective EIH (Xie et al., 2021). Participants will perform an exercise to evaluate EIH based on the group to which they were randomized (Table 2).

**FIGURE 2 eph13680-fig-0002:**
[figure not shown]
Illustration of the experimental procedure for assessing the acute effect. Pressure pain threshold (PPT) will be measured at points *X*, *Y*, and *Z* before and after the randomized exercise. Participants assigned to the specific exercise group will perform a lateral raise for 2 min or until fatigue. Participants assigned to the non‐specific exercise group will perform an isometric wall squat for 3 min or until fatigue.

**TABLE 2 eph13680-tbl-0002:** Description of the exercises that will be used to verify the acute effect of exercise through exercise‐induced hypoalgesia.

	Specific exercise group	Non‐specific exercise group
Exercise	[figure not shown]	[figure not shown]
	Lateral raise	Isometric wall squat
Duration	2 min or until fatigue	3 min or until fatigue
Instructions	The lateral raise will be performed with a light‐intensity elastic band. The participant will be instructed to perform the exercise in a controlled manner, taking approximately 2 s for both the raising and lowering phases (Andersen et al., 2011; Hansen et al., 2020). The participant will be guided to raise the arm to approximately 90° with the elbows slightly flexed. The exercise will be continued for the specified duration or until fatigue (Hansen et al., 2020).	The wall squat will be performed with the participant positioned against a wall, with feet parallel and hands at the side of the body. The knee flexion angle, measured with a goniometer aligned on the lateral epicondyle of the femur, should reach approximately 100° (Vaegter et al., 2019). Once positioned, participants will be prompted to sustain the crouched posture for the designated time or until muscle fatigue sets in. Pain intensity, measured by the Numeric Pain Rating Scale (NPRS), and perceived exertion will be recorded at the conclusion of the exercise (Smith et al., 2017).

#### Secondary outcomes

2.9.2

##### Pressure pain threshold

PPT will be measured using a digital pressure algometer (Algomed, Computerized Pressure Algometer, Medoc, Israel) positioned perpendicular to the skin with a pressure rate of approximately 40 kPa/s (Rampazo et al., 2020). A familiarization with an unrelated region (hand) will precede data collection (Andersen et al., 2012; Xie et al., 2021). All points are described in Table 3. Points will be randomized, and participants, with closed eyes, will press a button on the algometer with the hand contralateral to the evaluated limb and will be instructed to press it when the pressure stimulus becomes a clear sensation of pain. Three measurements will be taken at each point with a 30‐s interval between them (Walton et al., 2014), and the average will be used for analysis (Lluch et al., 2014). PPT in neck pain has good reliability with ICC = 0.89 for intrarater and 0.83 on test–retest, with a minimum detectable change (MDC) of 155.73 kPa and good responsiveness with area under the curve (AUC) = 0.76 (Walton et al., 2014).

**TABLE 3 eph13680-tbl-0003:** Description of the points that will be used in the pressure pain threshold.

Point	Description	Position
Bilaterally C2	2 cm laterally from the spinous processes of C2	Ventral decubitus with the face resting on the stretcher hole to keep the cervical spine neutral and arms along the body (Rampazo et al., 2021, 2020)
Bilaterally upper trapezius	Midway between the spinous process of C7 and the lateral edge of the acromion (Celenay et al., 2016; Rampazo et al., 2021)	Sitting on a chair with feet flat on the floor and trunk resting on the back of the chair (Rampazo et al., 2021, 2020)
Right anterior tibialis	Middle third of the right tibialis anterior muscle (Hansen et al., 2020; Rampazo et al., 2021)	Dorsal decubitus with knees bent and feet resting on the stretcher (Walton et al., 2011)
Right low back	5 cm laterally from the spinous process of L3 (van Oosterwijck et al., 2012)	Prone position with arms along the body (van Oosterwijck et al., 2012)
Left quadriceps femoris muscle	20 cm above the center of the left patella (Hansen et al., 2020; Vaegter et al., 2014).	Supine position with a pillow under the knee (Hansen et al., 2020)

##### Temporal summation of pain

Temporal summation of pain (TSP) will be evaluated at the right upper trapezius. Ten pressure stimuli will be applied at the previously determined pressure value, with a 1 s interval between them. Participants will quantify pain intensity for the first, fifth and tenth stimuli using the NPRS (Corrêa et al., 2016). The difference between the tenth pain intensity stimuli and the first will be used for analysis. TSP has demonstrated good reliability with ICC = 0.75 (Cathcart et al., 2009).

##### Conditioned pain modulation

Conditioned pain modulation (CPM) will be evaluated using a cold conditioning stimulus test, with the PPT at the left upper trapezius and right quadriceps femoris points as the test stimulus. Participants will be instructed to immerse their right foot (up to the ankle) in a bucket of ice water at 4°C for 1 min (Shahidi & Maluf, 2017). Before removing the foot from the water, participants will rate the pain intensity in the foot based on the NPRS (Vaegter et al., 2014; Yarnitsky et al., 2015). After 1 min, they will remove their foot from the water to avoid distraction bias, and PPT on the upper trapezius and quadriceps femoris will be measured again (Valencia et al., 2013; Yarnitsky et al., 2015). The values obtained before and after immersion will be subtracted (PPT after the conditioning stimulus minus PPT before the conditioning stimulus) to evaluate the effectiveness of CPM. A positive value reflects CPM, and the higher the value, the more efficient the endogenous pain inhibition (Xie et al., 2021). Data will be reported in absolute difference, as recommended in the literature (Kennedy et al., 2016).

##### Neck Disability Index

The NDI will be used to assess disability of patients with neck pain. The translated and validated version for Brazilian Portuguese (Cook et al., 2006) demonstrated good internal consistency and reliability (Cook et al., 2006). The NDI consists of 10 questions rated from 0 (no disability) to 5 (greater disability). The total score is expressed as a percentage of the maximum possible score according to the number of questions answered (Chung & Jeong, 2018). The MDC is 10.5 points (Pool et al., 2007) while the MCID is 7 points, both on a scale of 0–50 (Abbott & Schmitt, 2014).

##### Global Rating of Change

The Global Rating of Change (GROC) will be used to assess the global perception of change after the 8‐week intervention and at the 6‐month follow‐up. The GROC is a 15‐point scale ranging from −7 (a very great deal worse) to 0 (about the same) to +7 (a very great deal better). It will be used to quantify a patient's improvement with treatment (Kamper et al., 2009). It has excellent reliability (ICC between 0.80 and 0.92) on test–retest (Bobos et al., 2019) and is considered a valid reference standard for identifying clinically important changes (Cleland et al., 2007). A score of +4 will indicate positive improvement (Cleland et al., 2007), with the MCID set at a 3‐point difference from the baseline (Daher et al., 2020). This scale will be collected in relation to cervical symptoms.

##### The Baecke Physical Activity Questionnaire

The Baecke Physical Activity Questionnaire (BPAQ) will assess the level of physical activity. This self‐reported questionnaire considers three indices of habitual physical activity (work, sports and leisure activities). Comprising 16 questions, the total score is the sum of all the questions (each rated from 0 to 5 points). A higher final score indicates a higher level of physical activity. It shows good reliability (Baecke et al., 1982; Silva et al., 2020) and is validated with the gold standard for the level of physical activity using the Doubly Labeled Water (Philippaerts et al., 1999).

The following will be also collected:
Exercise adherence: Participants will be given an adherence diary to fill in every week and also text messages will be sent to ask them about the exercise and adherence. Monthly calls or text messages, according to the participant's preference, will be made, to stay in touch with participants during the follow‐up period.Adverse events: In the weekly contact with the participant, questions regarding adverse events (such as pain, headache, dizziness or other symptoms that may occur) will be made and the answers will be registered.

### Sample size

2.10

The sample size was calculated using G*Power 3.1.9.7 based on analysis of variance (ANOVA) repeated‐measures, within–between interactions (two groups and three measurements). Thus, this study is designed to detect a small effect size (eta square of 0.02; Daher et al., 2020) in pain intensity. To detect this difference, 41 participants in each group are needed (assuming a power of 0.80, α level of 0.05 and critical *F* = 3.052). Considering a 15% dropout, the study will include 94 participants, with 47 in each group.

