### Statistical analysis

2.11

Patient characteristics at baseline will be reported with descriptive statistics as means and standard deviation (SD), median and interquartile range (IQR), or numbers and percentages as appropriate. Normality will be visually assessed using histograms and the Shapiro–Wilk test.

Using intention‐to‐treat analysis, treatment effects, differences between groups and confidence intervals (95%) will be calculated through repeated‐measures ANOVA, examining the interaction between treatment groups (SE and NSE) over time (baseline, post‐intervention, and 6‐month follow‐up). If the ANOVA results are statistically significant, univariate analysis will be conducted using the Tukey *post hoc* test, with Bonferroni adjustment for multiple comparisons. Effect size will be calculated using Cohen's *d*, categorized as small (0.02), medium (0.05), and large (0.08) (Cohen, 1988). IBM SPSS Statistics (Version 21.0; IBM Corp., Armonk, NY, USA) will be used for all analyses.

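### The 80% power described as being for a small effect is in fact power for a between-group difference of about 0.6 to 0.7 SD

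*Protocol article*

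**What the plan says.** The Sample size section (2.10) bases the calculation on an ANOVA for "repeated‐measures, within–between interactions (two groups and three measurements". It states that "this study is designed to detect a small effect size (eta square of 0.02", taken from a cited study, in pain intensity. It concludes that "41 participants in each group are needed", "assuming a power of 0.80, α level of 0.05 and critical" F of 3.052. It gives no correlation between visits, no G*Power effect-size option, and no target difference in SD units or pain-scale points.

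The Statistical analysis section (2.11) plans the matching test, "examining the interaction between treatment groups (SE and NSE) over time (baseline, post‐intervention, and 6‐month follow‐up", in SPSS, and says that effect sizes will be reported as Cohen's d. Strengths and limitations (3.2) lists the sample size among the study's strengths because it secures power for between-group differences in the primary outcome.

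**The concern.** Eta squared, Cohen's f and Cohen's d are different scales, and in a repeated-measures design the same eta squared can stand for very different mean differences. What it stands for depends on how it is defined and how strongly the visits correlate. A reader told that the trial has 80% power for a small effect will think of a small difference between the two exercise groups. If the calculation really rests on a moderate or larger difference, the article claims a sensitivity that the design lacks. A non-significant interaction could then be taken as evidence against a small advantage of either programme, which the trial would have had little chance of detecting.

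**Working it through.** **Inputs from the article:** 2 groups, m = 3 visits, eta squared 0.02, alpha 0.05, 41 per group (N = 82), critical F 3.052. **Assumed:** correlation rho between visits and sphericity. Rho = 0.5 is inferred because it reproduces the stated figures; 0.3 to 0.7 is also examined.

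**1. Reproducing the plan's figure.**
- f² = 0.02/0.98 = 0.0204, so f = 0.143.
- G*Power's default definition: lambda = f² × N × m/(1 − rho) = 0.0204 × 82 × 3/0.5 = 10.04.
- Degrees of freedom: 2 and (82 − 2) × 2 = 160. Critical F = 3.0525, as stated.
- Power = 0.809. With N = 80 it is 0.799, so 82 is the smallest even N that reaches 0.80.

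**2. Dependence on the correlation (same f, N = 82).**

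| rho | 0.3 | 0.4 | 0.5 | 0.6 | 0.7 |
|---|---|---|---|---|---|
| power | 0.66 | 0.73 | 0.81 | 0.89 | 0.96 |

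**3. The mean difference that this f represents.** In the default definition, f² is the average over the three visits of the squared interaction deviations, in units of the variance at one visit. Each deviation is half of the group difference at that visit after subtracting the mean difference over visits. Let d be the largest group difference in SD units, with none at baseline.
- Pattern (0, d, d) or (0, d, 0): f² = d²/18, so d = 0.1429 × √18 = 0.61.
- Pattern (0, d, d/2) or (0, d/2, d): f² = d²/24, so d = 0.1429 × √24 = 0.70.

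At rho = 0.5 the SD of change from baseline equals the SD at one visit, because √(2 × (1 − 0.5)) = 1. The figures therefore read the same for change scores. A simulation of 4,000 trials at 0.606 SD, pattern (0, d, d), rho 0.5 and 41 per group gave power 0.81.

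**4. The same target as a partial eta squared of the kind SPSS reports.** lambda/(lambda + 160) = 10.04/170.04 = 0.059.

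**5. Power for smaller differences,** pattern (0, d, d), rho 0.5, lambda = (d²/18) × 82 × 3/0.5.

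| d (SD) | 0.2 | 0.3 | 0.4 | 0.5 | 0.61 |
|---|---|---|---|---|---|
| power | 0.14 | 0.27 | 0.44 | 0.64 | 0.81 |

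**6. In pain-scale points.** The article gives no SD. With an assumed SD of 2, 0.61 to 0.70 SD is 1.2 to 1.4 points. Over an assumed SD of 1.5 to 2.5, the range is 0.606 × 1.5 = 0.9 to 0.700 × 2.5 = 1.75 points.

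**7. Conditional check.** Suppose the cited 0.02 is a partial eta squared from ANOVA output. It then already contains the correlation, and lambda = f² × (N − 2) × (m − 1) = 0.0204 × 160 = 3.27. Power at N = 82 would be 0.34, and 80% power would need about 240 evaluable participants (120 per group).

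**The case against.** **The calculation is correct as run.** This stands in full. The named software, test and inputs return 41 per group and the stated critical F. A reader might infer an arithmetic error, or that 41 per group fails to give 80% power for an eta squared of 0.02. The document supports neither: under the default definition, 0.02 is what the calculation used, and power is 0.81.

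**A reader might infer that true power is 34%.** That holds only if the cited 0.02 is a partial eta squared from ANOVA output. The article does not say which kind it is, and the source is not at hand. The planned use of SPSS concerns the analysis of this trial and says nothing about where 0.02 came from.

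**A reader might take the critical F as proof of a gap.** F(2,160) = 3.0525 equals a partial eta squared of 6.105/166.105 = 0.037, and an observed 0.02 would give F = 1.63, p = 0.20. This is not independent evidence, because it presupposes the partial reading of 0.02. On that scale the planned effect is 0.059, above the 0.037 threshold, as 80% power requires.

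***Small* can be defended on the f scale, and the target lies below the clinical threshold.** By the usual conventions, f = 0.143 lies between small (0.10) and medium (0.25), nearer small. The section on pain intensity gives a minimal clinically important difference of 2.5 points, and 1.2 to 1.4 points is about half of that. Both are fair. They support the sample size as reasonable, but they do not make the label right on the d scale, and the Sample size section does not make this argument.

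**An article may omit the correlation and the effect-size option, and planned confidence intervals will show what a null result excludes.** Also fair. The omission is not the finding, and no passage says that a null result would rule out a small effect. What remains is that the article itself states 80% power for a small effect.

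**Conclusion.** The power target is misdescribed; the sample size is not miscalculated. Under the settings that reproduce the article's own figures (default effect definition, rho 0.5, sphericity), 41 completers per group give about 80% power for a difference in change of 0.61 to 0.70 SD, depending on its pattern over the two later visits. That is a partial eta squared of about 0.06. For differences that would ordinarily be called small on the d scale, power is about 14% (0.2 SD) to 27% (0.3 SD). The 80% also depends on rho: it would be 66% at 0.3 and 96% at 0.7. The 34% figure is a conditional side note until the kind of eta squared in the source is known. The point should be corrected, but it does not threaten the design.

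**What to change.** Reword the Sample size paragraph, for example:

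*Forty-one completers per group give about 80% power for a between-group difference of about 0.6 to 0.7 SD, depending on its pattern over the two later visits (about 1.2 to 1.4 points on the pain scale if the SD is 2, an assumption; below the 2.5-point minimal clinically important difference), assuming a correlation of 0.5 between visits and sphericity.*

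Drop *small*, and name the G*Power effect-size option used. Check in the cited source which kind of eta squared 0.02 is. Only if it is a partial eta squared from ANOVA output should the stated power for it be corrected, to about 34%.

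The cost is one paragraph and a look at one reference. The stated sensitivity becomes less favourable, and this point requires no change in enrolment.

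### The abstract plans to randomise 110 participants and section 2.10 plans 94; nothing reconciles the two, and neither total matches the stated 15% dropout allowance

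*Protocol article*

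**What the plan says.** The abstract gives the size of the trial as "One hundred and ten participants aged between 18 and 65 years" and goes on to say that these people are randomised to the specific and non-specific exercise groups.

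Section 2.10 (Sample size) bases the number on pain intensity. It uses a repeated-measures ANOVA interaction with two groups and three measurements, an eta squared of 0.02, power 0.80 and alpha 0.05. It concludes that "41 participants in each group are needed", and then: "Considering a 15% dropout, the study will include 94 participants, with 47 in each group".

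No other section gives a total. Section 2.5 says that people are randomised once eligibility is confirmed and consent is given. Section 2.6 describes consecutively numbered envelopes but not how many.

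**The concern.** The planned number randomised should be a single figure, and this article prints two. The number of envelopes, the end of recruitment and any later judgement of whether the trial recruited to plan all depend on it. A reader of the results could not tell whether stopping at 94 was on target or 16 short, or whether reaching 110 was on target or 16 over. Section 3.2 counts the sample size determination among the study's strengths, and that claim needs one coherent number.

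The second, lesser matter is that the step from 41 to 47 per group does not deliver the 15% allowance it is said to contain.

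**Working it through.** **Inputs from section 2.10.** 41 per group (82 in total); dropout 15%; two groups, three measurements; eta squared 0.02; power 0.80; alpha 0.05; critical F 3.052; 94 to be included, 47 per group. From the abstract: 110.

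**Assumed, because not stated.** Correlation among repeated measures 0.5; nonsphericity correction 1.

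**1. Reproducing 41 per group.** The effect size is f² = 0.02/0.98 = 0.0204, so f = 0.143. The noncentrality is λ = f² x N x m/(1 − ρ), with m = 3 and ρ = 0.5, and the degrees of freedom are 2 and 2(N − 2). At N = 82, λ = 0.0204 x 82 x 3/0.5 ≈ 10.0, the critical F(2, 160) is 3.0525 and power is 0.809. At N = 80, power is 0.799. So 82 is the smallest even total that reaches 0.80, and both the 41 per group and the printed critical value are recovered. The starting calculation is not in question.

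The result depends strongly on the unstated correlation:

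| Correlation | Smallest even N for power 0.80 |
|---|---|
| 0.3 | 112 |
| 0.4 | 96 |
| 0.5 | 82 |
| 0.6 | 66 |
| 0.7 | 50 |

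**2. Reproducing 94.** Multiplying by (1 + d): 41 x 1.15 = 47.15 and 82 x 1.15 = 94.3. Rounded down, these are 47 and 94, the printed figures.

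**3. The inflation that gives the stated allowance.** If a fraction d is lost from those randomised, the number to randomise is n/(1 − d).

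- Per group: 41/0.85 = 48.2, so 49, which makes 98 in total.
- In total: 82/0.85 = 96.5, so 97, which becomes 98 with equal groups.
- Check: 49 x 0.85 = 41.65, at or above 41; 48 x 0.85 = 40.8, below it.

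**4. What each total covers.**

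| Randomised | Left after 15% loss | Per group | Largest loss that leaves 82 |
|---|---|---|---|
| 94 | 94 x 0.85 = 79.9 | 39.95 | 12/94 = 12.8% |
| 98 | 98 x 0.85 = 83.3 | 41.65 | 16/98 = 16.3% |
| 110 | 110 x 0.85 = 93.5 | 46.75 | 28/110 = 25.5% |

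**5. Power under the same assumptions.** 0.799 with 80 completers and 0.809 with 82. With no loss at all: 0.863 at 94 and 0.914 at 110.

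**6. Can 110 be derived or reconciled?** Neither form of 15% inflation applied to 82 gives it (94.3 or 96.5). It cannot be a screening number set against 94 randomised, because the abstract says that the 110 are themselves randomised.

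**The case against.** The strongest reply is that section 2.10 is the operative text and is clear in itself, so the abstract may simply carry a stale or different figure. That is possible, but the article does not say so, and a reader cannot know which number was corrected last. The contradiction stands.

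The reply carries more weight against the dropout point. The shortfall is about one completer per group, and the correction is two per arm. A planned 15% is itself approximate. Power of 0.799 is 0.80 at the precision that the section uses, and the gap from 0.809 is far smaller than the uncertainty from the unstated correlation, over which the required total runs from 112 to 50. I accept this: taken alone, the slip would be minor.

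The documents do not support four stronger readings that a reader might infer:

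- *The trial will finish below 41 per group.* This requires that 94 is the real target and that losses exceed 12.8%. At 110, a 15% loss leaves about 93, or 46 to 47 per group.
- *The stated power is not achieved.* At 80 completers it is 0.80 to two decimals, under assumptions that the article does not state.
- *Neither total follows from the inputs.* The 94 does follow from them, by the wrong inflation formula. Only 110 has no stated derivation.
- *Recruitment can be stopped at will.* Two published targets make it hard to show that stopping was as planned. But the article describes no interim look and does not give the list length, so the list may already be fixed.

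**Conclusion.** The article is wrong as written on its planned sample size: 110 in the abstract, 94 in section 2.10, a difference of 16, with no reconciliation. This rests on the printed figures alone and needs no modelling assumption. It should be corrected, because the total is a figure on which the conduct and reporting of the trial rely.

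The inflation error is real but minor, and it matters only if 94 is the target. In that case the true allowance is 12.8%, and a 15% loss would leave about 40 per group. The power figures rest on a correlation of 0.5 and sphericity. The allowances of 12.8% and 25.5% depend only on the stated 82.

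**What to change.** State one target in both the abstract and section 2.10, with the dropout allowance it really provides:

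- 94 (47 per group), described as covering 12.8% dropout;
- 110 (55 per group), described as covering about 25% dropout, or with its actual basis if that is something else; or
- 98 (49 per group), if 15% dropout and 41 per group are both to be kept.

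Set the randomisation list and the envelopes to that number. Stating the correlation and sphericity values used in the calculation would let a reader repeat it.

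Keeping 94 or 110 costs wording only. Moving to 98 costs four participants more than section 2.10 plans (98 − 94).
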